#### Secondary outcome measures

Secondary outcome variables in this study are: alcohol use (TLFB), depressive symptoms (CES-D) and quality of life. Alcohol use is measured in addition to the 7-day TLFB with the AUDIT [62, 68]. The AUDIT is a 10-item questionnaire that measures alcohol use and related burden in the past year and has shown good psychometric properties to detect early AUD in university students [68, 69] as well as in the general population [70]. The AUDIT identifies hazardous, harmful and dependent drinking patterns, depending on certain cut-of scores. Typically total scores of ≥8 indicates hazardous and harmful alcohol use, although frequently lower and different cut-off scores are suggested, depending on the type of population [68]. We use cut-off scores of ≥5 for women and ≥ 8 for men, based on the Dutch multidisciplinary guideline for AUD [71]. Quality of life will be measured with both the five-level variant of the five-dimensional EuroQol instrument (EQ-5D-5L) and with a Dutch translation of the MOS SF-36 (i.e. RAND-36 item Health Survey) [72].

#### Other variables of interest

Various other variables will be assessed. See Table 2 for an overview of all measurement instruments and assessment timepoints.
*Socio-demographic information:* General patient characteristics will be collected at baseline, these include: gender, age, marital status, employment status, education level and ethnicity.*Drinking motives:* Motives for drinking alcohol will be assessed with the Drinking Motives Questionnaire Revised (DMQ-R) [73]. The DMQ-R is widely used for assessing drinking motives among young populations. The 20-item questionnaire assesses motives for drinking on four factors: enhancing (e.g. drinking because it is fun) coping (e.g. drinking to forget worries), confirmative (e.g. drinking to be liked) and social motives (e.g. drinking to be sociable) [74]. The DMQ-R has shown to be acceptable for measuring drinking motives in adults with mood and anxiety disorders and appropriate for Dutch general adult population [74, 75].*General Mental Health:* General mental health is measured with the brief 5-item Mental Health Inventory (MHI-5) [76]. The MHI-5 is a subscale from the MOS SF-36 and has shown to be a good screener for mood disorders in the general population [77].*Patient satisfaction:* Participants’ treatment satisfaction is measured with a Dutch version of the 8-item Zufriedenheid (ZUF-8) questionnaire, scores range between 8 and 32, higher scores indicate more satisfaction with the received treatment [78, 79].*Intervention uptake:* Intervention uptake is measured through log data from the digital alcohol moderation intervention, for example by the number of times participants logged in, the number of completed modules and program duration.*Healthcare utilisation and productivity costs:* Assessment of healthcare costs and productivity losses or gains will be measured with the TIC-P (Trimbos/iMTA questionnaire on Costs associated with Psychiatric illness) a reliable instrument for collecting health care utilization and productivity loss [80].*Anxiety symptoms:* Anxiety symptoms will be measured with the brief 7-item Generalized Anxiety Disorder (GAD-7). Total scores range from 0 to 21, higher scores indicate a higher level of anxiety severity, cut-off points of 5, 10 and 15 indicate levels of mild, moderate and severe levels of anxiety respectively [81]. A meta-analysis has found the GAD-7 to be accurate in identifying generalized anxiety disorder and also any anxiety disorder, with high sensitivity and specificity values when using a cut-off point of 8 [82].*Traumatic events and post-traumatic stress symptoms:* Traumatic events and post-traumatic stress symptoms are assessed with the Dutch Childhood Trauma Questionnaire – Short Form (CTQ-SF) and Post-traumatic Stress Disorder Checklist for DSM-5 (PCL-5) [83, 84]. The CTQ-SF is a 28-item questionnaire that assesses five dimensions of childhood maltreatment: physical abuse, emotional abuse, sexual abuse, physical neglect and emotional neglect [85]. The Dutch CTQ-SF has been found to have adequate internal consistency and reliability. The 20-item PCL-5 questionnaire is widely used to screen for symptoms of post-traumatic stress disorder in the past month [86]. Several studies have found that the PCL-5 has good psychometric properties [84, 86]*Emotion dysregulation:* The widely used Difficulties in Emotion Regulation Scale (DERS-18) will be used to assess difficulties in emotion dysregulation [87]. The DERS-18 is an 18-item short form and has shown good internal consistency and convergent validity in populations with emotional disorders [87].*Resilience:* Psychological resilience will be measured with the brief Dutch 9-item Resilience Evaluation Scale (RES). The RES measures two constructs underlying resilience, that is self-confidence and self-efficacy. The instrument is used in various studies and has shown good psychometric properties [88].*Borderline personality features:* The 24-item Personality Assessment Inventory-Borderline Features (PAI-BOR) scale will be used to assess borderline features. The PAI-BOR questionnaire screens for borderline personality disorder features [89].*Perceived impact of COVID-19 measures:* We used a self-constructed 7-item questionnaire to assess the impact of COVID-19 and related measures on the participants’ depressive symptoms, alcohol use and study participation. The questions assess to what extent the pandemic led to either an increase, decrease or had no impact on depressive symptoms and alcohol consmption and what the reasons for the in-or decrease were. One question assessed whether the pandemic and restricting measures had an influence on any attempts of reducing alcohol use. Lastly, two questions assessed whether the pandemic had any influence on study participation and if so, for which reasons.

**Table 2 Tab2:** Schedule of enrollment, allocation, interventions, and assessments

	Enrollment	Baseline	Allocation	Follow-up		
	*t*_*-1*_	*t*_*0*_		*t*_*1*_	*t*_*2*_	*t*_*3*_
**Enrollment**						
Eligibility screen	**X**					
Informed consent	**X**					
Baseline assessment		**X**				
Allocation			**X**			
**Interventions**						
TAU + BtB			**X**	**X**	**X**	
TAU			**X**	**X**	**X**	
**Assessments**						
Socio-demographic characteristics		**X**				
TLFB		**X**		**X**	**X**	**X**
AUDIT		**X**		**X**	**X**	**X**
CES-D		**X**		**X**	**X**	**X**
EQ-5D-5L		**X**		**X**	**X**	**X**
RAND-36		**X**		**X**	**X**	**X**
DMQ-R		**X**		**X**	**X**	
MHI-5		**X**		**X**	**X**	**X**
ZUF-8				**X**		
TIC-P		**X**		**X**	**X**	**X**
DERS-18		**X**			**X**	
GAD-7		**X**			**X**	
PAI-BOR		**X**			**X**	
CTQ-SF		**X**				
PCL-5		**X**			**X**	
RES		**X**			**X**	
Impact COVID-19		**X**		**X**	**X**	**X**

*TAU + BtB* Treatment as usual + Beating the Booze, *TAU* Treatment as usual, *TLFB* Timeline Followback, *AUDIT* Alcohol Use Disorder Identification Test, *CES-D* Center for Epidemiological Studies-Depression, *EQ-5D-5L* five-level and five-dimensional EuroQol, *RAND-36* RAND-36 item Health Survey, *DMQ-R* Drinking Motives Questionnaire Revised*, MHI-5* Mental Health Inventory, *ZUF-8* Zufriedenheid questionnaire, *TIC-P* Trimbos/iMTA questionnaire on Costs associated with Psychiatric illness, *DERS-18* Difficulties in Emotion Regulation Scale, *GAD-7* Generalized Anxiety disorder, *PAI-BOR* Personality Assessment Inventory-Borderline Features scale, *CTQ-SF* Childhood Trauma Questionnaire – Short Form, *PCL-5* Post-traumatic stress disorder Checklist for DSM-5, *RES* Resilience Evaluation Scale

### COVID-19 pandemic

Participant recruitment and data collection was partly conducted during the COVID-19 pandemic and the restricting measures, such as periods of social distancing and lockdowns. We have added a COVID-19 questionnaire to the assessments to assess the influence of these restrictions on the primary outcome of the trial. The questionnaire assesses the perceived impact of the pandemic on the participants’ current alcohol use, depressive symptoms and study participation. The external influence of COVID-19 on the primary outcomes will be accounted for in the analysis.

### Data analysis

#### Effectiveness

The primary outcome variable is treatment response, which indicates whether the treatment has been successful or not. We will use Generalized Linear Mixed Models (GLMM) with link functions, depending on the data types and distributions of the dependent variables. For the analyses of the intervention outcomes, we will use count/continuous data in case of alcohol use and dichotomous data in case of treatment response. We used stratified randomization for participating site and we will include the stratas in the GLMM analysis as covariates. Missing data will be handled by using multiple imputation methods. Analyses will be conducted based on intention-to-treat principles and additional sensitivity analyses will be conducted on a protocol/treatment completers sample. All analyses will be carried out using SPSS version 26+ and/or R version 3.0 + .

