### Participants

The target population consists of Dutch young adults with a depressive disorder, 18 to 35 years old, who drink alcohol at least at hazardous levels and receive outpatient treatment for a depressive disorder. Participants will be recruited at three participating sites of Arkin Mental Health Care (the Netherlands) and through social media advertisements. Patients are eligible to participate in the study if they meet the following inclusion criteria: (1) between 18 and 35 years old, (2) diagnosed with a depressive disorder and either enrolling for treatment or currently in treatment (3) a score of ≥8 for men and ≥ 5 for women on the Alcohol Use Disorders Identification Test (AUDIT), (4) at least moderately proficient in Dutch, (5) willingness to provide contact details, (6) healthcare insurance coverage, (7) access to a computer or mobile device and (8) providing informed consent. Potential participants are excluded from study participation in case of: (1) acute psychosis, (2) having a primary diagnosis of severe AUD, (3) dementia, (4) (waitlisted for) in-patient mental health care or (5) pregnancy.

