### Sample size

We used R package ‘pwr’ to calculate the sample size with α = .05 (two-sided) and Power (1-β) = .80 [56]. We aim to include a total of 156 participants to detect a 25%-point treatment effect difference between experimental and control groups (i.e. treatment response of 50 and 25%, respectively). Sample size is calculated by taking into account 35% extra inclusion to account for drop-out and the design effect (multicentre clustering).

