### Outcome measures

#### Primary outcome measure

The primary outcome is treatment response (yes/no) and is measured at 6-month follow-up which is the primary endpoint of the RCT. The treatment response outcome combines an alcohol use measure and a depression-related measure into a composite score. Alcohol use will be measured with the self-administered 7-day Timeline Followback (TLFB) methodology [62]. The TLFB is a frequently and widely used retrospective calendar method of assessing daily alcohol use estimates in a certain period of time (e.g. 7 or 30 days). The self-administered web-based 30-day TLFB on drinking has shown strong psychometric properties among young adults and research suggests that the 7-day TLFB may be more accurate in assessing volume and timing of consumption compared to the 30-day TLFB due to longer-recall periods [63, 64]. In addition, there is evidence supporting that individuals may feel more comfortable completing the TLFB online [65]. Depression is measured with the brief 20-item self-report Center for Epidemiological Studies-Depression (CES-D) and measures current depression symptoms a week prior to assessment. CES-D scores range between 0 (best possible) and 60 (worst), a cut-off point of 16 is often recommended for detecting depression [66]. The CES-D has acceptable screening accuracy in both general population and primary care settings [67]. Treatment is deemed successful (i.e. treatment response) if all following three conditions are met: (1) drinking less than 21 (males) or 14 (females) glasses of alcohol in the week prior to measurement, (2) 0 days with 4 or more (women), or 5 or more (men) drinks reported in the last 7 days and (3) a CES-D depression score of < 16 or a reduction of 40% relative to CES-D at baseline. Glasses are in this study defined as standard drinks which contain 10 g of ethanol (the European standard).

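### The treatment-response model names the randomisation strata but no baseline severity, so it forgoes precision that is free; separately, the composite can already be met at baseline, which adjustment does not cure

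*Protocol article*

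**What the plan says.** Data analysis, Effectiveness: the dichotomous treatment response is analysed by a generalised linear mixed model, and the covariates named are the strata: "We used stratified randomization for participating site and we will include the stratas in the GLMM analysis as covariates". The COVID-19 pandemic section adds that the influence of COVID-19 will be accounted for, without saying how. No baseline severity measure is named in either place.

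Primary outcome measure: response at 6 months needs three conditions together.
- Weekly volume: "drinking less than 21 (males) or 14 (females) glasses of alcohol in the week prior to measurement".
- No day in the last 7 with 4 or more drinks (women) or 5 or more (men).
- CES-D below 16, or 40% lower than at baseline.

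Participants: alcohol entry rests on an AUDIT score of at least 8 (men) or 5 (women). Secondary outcome measures says that the AUDIT covers the past year. Depression entry rests on a diagnosis, in people "either enrolling for treatment or currently in treatment". No minimum 7-day consumption and no minimum CES-D is listed.

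Table 2 shows TLFB and CES-D at baseline, and Randomization and follow-up assessment places allocation after the baseline assessment. The sample size uses "α = .05 (two-sided) and Power (1-β) = .80" with "treatment response of 50 and 25%, respectively".

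**The concern.** The baseline values of the endpoint's own components are in hand before allocation, yet the stated model does not use them. How far a participant must improve depends on the starting point. At a baseline CES-D of 16 a one-point fall meets the third condition. At a baseline of 40 the score must fall by 0.40 × 40 = 16 points, to 24. The alcohol conditions are the same 7-day measure taken six months later. It is reasonable to expect baseline values to predict response, and a prognostic covariate in the model usually sharpens the treatment comparison. The same response is also the effect measure in the cost-effectiveness analysis, so imprecision carries over to it.

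A second question is what a response means. Two conditions are absolute, and the third can be met absolutely. Someone can therefore satisfy them on entry and again at 6 months. Such participants leave the intervention less room to move the composite.

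**Working it through.** **1. The plan's own figure.** Inputs from Sample size and Randomization: 25% against 50%, two-sided α = 0.05, power 0.80, 1:1 allocation, 35% extra inclusion.

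Arcsine effect size, as in the pwr package: h = 2·arcsin(√0.50) − 2·arcsin(√0.25) = 0.5236. Then n = 2 × ((1.960 + 0.842)/0.5236)² = 57.26, rounded up to 58 per arm and 116 in total. 116 × 1.35 = 156.6, against the stated 156. The figure reproduces, and it comes from an unadjusted comparison of two proportions. Power is 80.2% with 58 per arm analysed and 90.5% if all 78 per arm are analysed.

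**2. What adjustment could add.** The article gives no prognostic strength for baseline TLFB or CES-D, so a range is assumed. Simulation: 3,000 trials per row, 58 per arm, one standard-normal baseline score, marginal rates held at 25% and 50%, likelihood-ratio test of treatment in a logistic model. Simulation error is about 0.7 points.

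| Baseline score: AUC for response (assumed) | Power, unadjusted | Power, adjusted | Conditional odds ratio |
|---|---|---|---|
| 0.50 (no value) | 81% | 81% | exp(1.099) = 3.0 |
| 0.61 | 80% | 83% | exp(1.137) = 3.1 |
| 0.70 | 80% | 85% | exp(1.243) = 3.5 |
| 0.78 | 80% | 89% | exp(1.396) = 4.0 |
| 0.83 | 82% | 93% | exp(1.579) = 4.8 |

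The gain runs from about 0 to 10 points. The last column shows why the reported measure matters: for the same 25% and 50%, the conditional odds ratio grows with the covariate's strength, while the risk difference stays at 25 points.

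**3. The fuller model.** With three baseline covariates and the four strata (three sites and the social media group), also at 58 per arm, simulated power was 0.83, 0.86 and 0.89 for assumed latent correlations of 0.3, 0.5 and 0.6. Without the baseline covariates it was about 0.80 to 0.81. Type I error stayed near 5%.

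**4. Who can respond without change.**
- Both alcohol conditions: anyone with a light baseline week, whatever the past-year AUDIT score.
- The whole composite: only someone who also has a baseline CES-D below 16.
- With a baseline CES-D of 16 or more: not possible, because the third condition then requires improvement.

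**5. Dilution, as illustration only.** The documents give no share of participants who meet any condition at baseline. Two assumed models at 58 per arm:
- A share f meets the alcohol conditions at entry and gains nothing, so the difference is 25 × (1 − f) points. For f = 10%, 20% and 30% it is 22.5, 20 and 17.5 points, with arcsine power 0.72, 0.63 and 0.52.
- A share b meets the whole composite at entry and responds at 80% in both arms, and the rest respond at 25% and 50%. For b = 10% the rates are 0.25 × 0.9 + 0.8 × 0.1 = 30.5% and 0.50 × 0.9 + 0.8 × 0.1 = 53.0%. Power is 75%, 70% and 58% for b = 5%, 10% and 20%.

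**The case against.** **The strata need not be the whole list.** A reader might infer that the model adjusts for strata and nothing else. The text does not say so: the COVID-19 section announces a further adjustment, and an analysis plan that is not shown may name more covariates. This stands, and it is why the point is an improvement to the stated model and not an error in it.

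**No planned power is lost.** A reader might infer a shortfall. There is none, because 156 was derived without adjustment. Nor is chance imbalance at baseline a bias: randomisation balances baseline status in expectation, and the unadjusted test allows for chance. This also stands.

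**Too many covariates for the events.** At 116 evaluable and a pooled response of 37.5% there are about 43 responders for seven non-intercept terms: treatment, three stratum contrasts and three baseline covariates. Two of the three baseline covariates come from the same TLFB week. The caution is fair, but the fuller simulation kept the gain and an acceptable type I error.

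**Response without change may be rare.** The whole composite can be met at entry only with a CES-D below 16, in people with a diagnosed depressive disorder. Recruitment also narrows the already-treated group: social media recruits have recently started or will soon start treatment, and site recruits are invited to baseline around the start of theirs. The app addresses depression and relapse prevention too, so people already within the alcohol limits may still benefit. The 25% and 50% were set for the whole trial population, so applying them only to the others is an added assumption. All of this limits what can be said about size. It does not remove the possibility, which follows from the entry criteria and the response definition.

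**Secondary models.** Outcomes are measured at every visit, and a repeated-measures model may already include baseline. The article does not say.

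**Conclusion.** The point holds as a free gain in precision. The article names the strata and an unspecified COVID-19 adjustment but no baseline severity, although the baseline components of the composite are available before allocation. The gain is about 0 to 10 points of power at 58 per arm. That range rests wholly on assumed prognostic strength, and the unadjusted analysis keeps its planned 80%.

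Response without change is a separate matter. It arises from absolute response conditions combined with entry criteria that set no 7-day drinking or CES-D floor. Covariate adjustment reclassifies nobody and restores no diluted effect. A reader might infer from the dilution figures that the trial is underpowered. The documents do not support that, because the shares of 5% to 30% and the response assumed in those participants are illustrations.

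**What to change.** 1. In the primary model, next to the strata, add baseline TLFB weekly drinks and baseline CES-D. Baseline heavy-drinking days are optional.
2. Adjust each secondary model for its own baseline value, unless the repeated-measures model already does so, and state which applies.
3. Report the primary result as a standardised (marginal) risk difference at 6 months with its confidence interval. That is the scale of the 25-point planning effect.
4. Pre-specify one supportive analysis in participants who fail at least one of the three conditions at baseline. For this purpose the third condition is read as CES-D below 16, since no reduction from baseline exists yet. The subset is defined by pre-randomisation data, so the comparison within it remains randomised. Report the share who meet each condition at baseline, by arm.

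The cost is wording in the analysis section, with no new data and no extra participants. The text should be settled before outcomes by arm are seen, because covariates chosen afterwards invite selective reporting.

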#### Duration

Previous research implies that participants do not always have to complete all of the available elements of a digital intervention to achieve beneficial effects. Participants also might have different effective usage patterns and thus might use different intervention elements compared to other participants depending on their personal goal [60]. The duration of BtB will vary for every participant since the program can be completed in the participants own pace. At fastest, that is the minimal duration of completion of all modules, is 18 days. We however advise participants to complete every module within 1 or 2 weeks. The combined treatment, including TAU + BtB has a per-protocol duration of 4–6 months.

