The current study has several strengths and challenges. Our trial is designed as a pragmatic RCT and aims to evaluate the (cost-)effectiveness of the add-on digital alcohol moderation intervention to treatment as usual for depressive disorders. Pragmatic trials often have higher external validity and generalizability because of conducting the trial in normal clinical practice settings and by using less strict in-and exclusion criteria. Such trial designs therefore often have lower internal validity compared to traditional explanatory RCTs [93]. However, a pragmatic trial design is the most suitable design considering our research aim and the economic evaluation that is conducted alongside the trial. Other strengths of the current study include a multi-centre RCT design, a 12-month follow-up, a relatively large sample size, insight in the (cost-)effectiveness of the combined alcohol and depression treatment for young adults and lastly a novel digital add-on alcohol moderation intervention that was developed through co-creation with expert patients and based on a former and existing web-based alcohol self-help which was found effective among problem drinkers [59]. A common challenge in the field of digital interventions is poor treatment adherence and high dropout rates [94]. Literature shows that guidance can enhance adherence and increase effectiveness compared to completely unguided digital interventions [32, 94]. Thus, minimal asynchronous adherence-focused guidance will be provided by a coach, who will be available for questions and will motivate users to complete the alcohol moderation modules after certain periods of inactivity in the program. Additionally, automatic e-mail reminders will be sent to users after inactivity in the digital intervention. Study drop-out is prevented by giving participants a monetary compensation for every completed follow-up assessment. Completion of follow-up assessments is facilitated by giving participants the opportunity to fill out questionnaires online and on any mobile device. Another challenge for the current study is the COVID-19 pandemic and the corresponding restricting measures that were taken by the Dutch government, such as lockdowns and social distancing. Preliminary research suggest that the COVID-19 pandemic and the restricting measures influence, both negatively and in some circumstances positively, alcohol use and depressive symptoms [95–100]. Therefore, they might also influence the outcomes of the current study. In order to assess the perceived impact of these COVID-19 related measures on both alcohol use and depressive symptoms of study participants, we have added COVID-19-specific items to our online assessments.

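### The only sensitivity analysis named for effectiveness is a completers sample, which selects after randomisation and cannot apply the same filter in both arms if completion includes the app

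*Protocol article*

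**What the plan says.** The protocol article, Data analysis, Effectiveness, plans generalised linear mixed models with the randomisation strata as covariates, multiple imputation for missing data, and intention-to-treat as the basis. It then says that "additional sensitivity analyses will be conducted on a protocol/treatment completers sample". This is the only sensitivity analysis named for effectiveness. The one-way analyses under Cost-effectiveness calculations concern cost drivers.

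The article does not define a completer in either arm. Four other places bear on the point:

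- **Treatment as usual (TAU):** both arms receive it. Only the experimental arm also receives the app.
- **Duration:** the app is self-paced, and the term per-protocol is attached to the combined treatment, TAU plus app. The section also says: "Previous research implies that participants do not always have to complete all of the available elements of a digital intervention to achieve beneficial effects".
- **Other variables of interest:** uptake is taken from log data, for example "the number of times participants logged in, the number of completed modules and program duration".
- **Discussion:** "A common challenge in the field of digital interventions is poor treatment adherence and high dropout rates". No expected rate is given for this trial.

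**The concern.** A sensitivity analysis should ask whether the main result survives a change in an assumption behind it. A completers sample asks something else. It keeps people according to what they did after allocation, so the groups compared are no longer those that randomisation made comparable.

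The problem is sharper here because the treatments differ. Finishing a self-paced programme is the participant's choice, and those who finish are plausibly more motivated. Controls have no modules to finish, so the equally motivated people among them cannot be picked out by the same rule. A difference in response can then arise with no effect of the app, and because it carries the label of a sensitivity analysis it may be cited as confirming the intention-to-treat result.

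The filter also fits poorly with the Duration section, which allows that partial users may benefit. A completers rule that requires the whole app would drop them.

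**Working it through.** **The plan's own figure.** The Sample size section gives "α = .05 (two-sided) and Power (1-β) = .80" and "treatment response of 50 and 25%, respectively". With the arcsine effect size, h = 2·asin(√0.50) − 2·asin(√0.25) = 0.5236, and n = 2·((1.960 + 0.842)/0.5236)² = 57.3, so 58 per arm. Adding 35% gives 2 × 58 × 1.35 = 156.6, which agrees with the stated 156. No stated number is in dispute. The 25% control response is used below.

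**Selection bias under no effect, all controls kept.** Let c be the share of the experimental arm who complete and r the ratio of completers' to non-completers' response. Neither is in the document, so both are assumed. Overall response is held at 25% in each arm:

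- non-completers' response: p_n = 0.25 / (c·r + 1 − c)
- completers' response: p_c = r·p_n
- spurious difference: p_c − 0.25

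| c | r | p_n | p_c | Spurious difference (points) |
|---|---|---|---|---|
| 0.30 | 1.5 | 21.7% | 32.6% | 7.6 |
| 0.30 | 2.0 | 19.2% | 38.5% | 13.5 |
| 0.40 | 1.5 | 20.8% | 31.3% | 6.3 |
| 0.40 | 2.0 | 17.9% | 35.7% | 10.7 |
| 0.40 | 2.67 | 15.0% | 40.0% | 15.0 |
| 0.50 | 1.5 | 20.0% | 30.0% | 5.0 |
| 0.50 | 2.0 | 16.7% | 33.3% | 8.3 |
| 0.70 | 1.5 | 18.5% | 27.8% | 2.8 |
| 0.70 | 2.0 | 14.7% | 29.4% | 4.4 |

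The range is 2.8 to 15 points, against the 25 points the trial is designed to detect. The bias grows as completion falls. In every row the intention-to-treat difference is 0, and so is a complier-average estimate, for example 0/0.40 = 0.

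**Controls limited to TAU completers.** The document gives nothing from which to size this case. One assumed example shows that the bias need not vanish. In each arm 75% complete TAU and respond at 30%, and the other 25% respond at 10%: 0.75 × 0.30 + 0.25 × 0.10 = 0.25. If 40% of the experimental arm complete both TAU and app and respond at 40%, the contrast is 40% against 30%, a false 10 points. A filter on TAU alone, unaffected by the app, would avoid this under no effect, but the text does not specify one.

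**Why the adherence definition matters for a complier-average analysis.** The estimate is the intention-to-treat difference divided by the share counted as adherent. It assumes that the offer has no effect on anyone not counted (the exclusion restriction). Suppose 40% finish and gain 15 points, while 60% use part of the app and gain 10. Intention-to-treat is 0.4 × 15 + 0.6 × 10 = 12 points. With a threshold of all modules completed, the estimate is 12/0.4 = 30, double the finishers' true gain. With any use as the definition, everyone in this example is adherent and the estimate is 12/1 = 12, the correct average among users.

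**What a completers sample leaves untested.** If the whole 35% allowance were drop-out, about 1 − 58/78 = 26% of outcomes would be missing. Take 50% and 25% response among those observed, and let missing controls resemble observed ones. If missing experimental participants respond at 25%, the difference is 0.74 × 50 + 0.26 × 25 − 25 = 18.5 points. If none respond, it is 0.74 × 50 − 25 = 12 points. With 10% missing the two results are 22.5 and 20 points. Restricting to completers examines none of these cases.

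**The case against.** The strongest objection is that the text does not say what the sample is. A reader might infer that the plan compares app completers with all controls. The document does not support that: completion is undefined, controls receive a treatment that they too can complete, and per-protocol in the Duration section refers to the combined treatment. A completer definition is also something an article may leave to the full protocol or analysis plan. This stands, and it is why the size is conditional. It does not remove the point, because the selection on post-randomisation behaviour is stated, and any definition that includes the app filters the arms differently.

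A reader might also infer that the plan wrongly omits a test of the imputation assumption. That is not supported either. The article states no missingness assumption, and a delta-adjusted analysis may sit in a document not shown. Its absence from the article is not an error.

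Nor does the document say that low adherence is expected in this trial. The Discussion calls it a challenge of the field and describes guidance and reminders against it.

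Finally, the completers analysis is additional to intention-to-treat, such analyses are common, and nothing says that it will decide the conclusion. This limits the weight of the point. It does not make the contrast a sound robustness check.

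**Conclusion.** The point holds in limited form. The one sensitivity analysis named for effectiveness selects on behaviour after randomisation, and its filter cannot be the same in both arms if completion includes the app. Under no true effect, app completers against all controls would show a spurious gain of roughly 3 to 15 points. That range rests on assumed completion of 30 to 70% and assumed response ratios of 1.5 to 2. The upper end of 15 points needs a ratio of 2.67 at 40% completion. If controls are limited to TAU completers, the size cannot be derived from the document.

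The primary intention-to-treat result is unaffected. This is a cheap improvement to a supportive analysis and does not call the main inference into question.

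**What to change.** 1. Do not use the completers contrast as a robustness check on intention-to-treat. If it is kept, define completion for each arm before analysis and label it supplementary and non-randomised.
2. For the effect of using the app, specify a complier-average analysis with randomisation as instrument and the same strata covariates. Define adherence from the log data as any use, for example at least one login or one module started. A login is the safer of the two, because goal setting takes place at account registration, before the first module. Avoid a modules-completed threshold: the Duration section allows benefit from partial use, so such a threshold would breach the exclusion restriction.
3. Optionally, test the multiple imputation with a delta adjustment varied separately by arm, including missing counted as non-response.

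The cost is a few lines of analysis plan and code, since the log data are already collected. The complier estimate has wider confidence intervals: with 40% users, estimate and interval are both scaled by about 1/0.4 = 2.5. It still relies on the offer having no effect on those who never use the app, and if nearly everyone logs in once it will be close to the intention-to-treat estimate.
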